#### Participating regions and sample size estimation

(1) Group 1: Regions in Aomori, Akita, Iwate, and the Minamikyushu area, with a total population of 670,000 individuals.

(2) Group 2: Regions in Sendai, Chiba, and the Kitakyushu area, with a total population of 1,450,000 individuals.

After a preliminary survey to record the rate of suicidal behavior and other information in the target regions in these areas, intervention and control regions will be selected based on the similarity in community characteristics and the incidence of suicidal behavior (Figure 1).

**Figure 1 F1:**
[figure not shown]
Flow diagram of the study.

Each region has a designated regional leader. The personnel associated with each region include psychiatrists, researchers supporting community intervention, and personnel in charge of regional health administration.

#### Rationale for estimation of sample sizes

Sample sizes to be used in the study were calculated based on the assumptions of the outcome and suicide rates from 2002 to 2004 in Groups 1 and 2 presented in Table 1.

**Table 1 T1:** Assumptions of the outcome and suicide rates in Group 1 and Group 2

	Group 1	Group 2
Suicide rate in control regions (per 100,000 individuals)	30	20
Proportion of expected numbers of ambulance transports due to "self-harm" (severe and mild cases) relative to completed suicides	50%	50%
Expected suicide rate reduction over observed 3 years by intervention	20%	15%
Significance level (two-sided)	5%	5%

*Notes*. These assumptions of the outcome and suicide rates (2002–2004) are used to calculate the sample sizes in this study.

Group1: regions with a relatively high suicide rate compared to control regions, examined to gauge the effectiveness of the community-based multimodal intervention program for suicide prevention.

Group 2: highly-populated regions, examined in order to explore the effectiveness of the community-based multimodal intervention program for suicide prevention.

Although the estimated sample sizes are not adjusted for 5-year age group, sex, and regional characteristics, if all assumptions are met, the statistical power will be over 80% for each group, regarding person-year incidences in the intervention and control regions.

Using the O'Brien-Fleming method [12] in the interim analysis, the significance level in the final analysis is estimated to be 4.9% for a two-sided test. In addition, the statistical power will be over 80% in each group.

### Intervention

The intervention program will be implemented by local authorities.

#### Suicide prevention program in control regions

The interventions in the control regions include the usual suicide prevention programs.

#### Suicide prevention programs in intervention regions

The local health authorities will implement the suicide prevention measures in accordance with the intervention manual developed by the program committee of the study group. To better enhance the quality of the essential intervention activities, the local health authority is also requested to share with the other study group members the information on the program tools.

##### The program components

The program stresses that bonds between human beings, social support, and social capital within communities are key factors for reducing suicide. Its essential components are listed below.

(1) The program focuses on building social support networks in the public health system for suicide prevention and mental health promotion, which will reinforce human relationships in the community.

- Network meetings of related departments and organizations will be held.

- Coordinating committees for the program will be formed in the intervention regions.

(2) Primary prevention measures for suicide and suicide-related behavior

- An public awareness campaign will be set up.

- Community programs will be set up to allow residents to gather and communicate.

(3) Secondary prevention measures for suicide and suicide-related behavior

- High-risk individuals will be screened.

- Counseling and outreach services will be provided.

(4) After-care for individuals bereaved by suicide

(5) Suicide prevention measures targeting individuals with substance/alcohol-related disorders, schizophrenia, and other mental health disorders

(6) Suicide prevention measures targeting individuals with work-related problems.

### Study period

Study period: August 2005 to March 2010.

Intervention period: July 2006 to December 2009.

### Approval of the study protocol

This study protocol was reviewed and approved by the Central Research Ethics Committee of the J-MISP. Additionally, the regional leaders will ask the local governors for cooperation, and obtain written authorization to conduct the study. Regional leaders will obtain approval from the ethics committees of affiliated universities or hospitals.

### Data collection

#### Baseline Information

Data will be collected for the items below:

##### (1) Statistics on suicide

The number of suicides in the 3 years prior to the study (2003–2005) in the study regions was recorded by sex and 5-year age group the Japan Ministry of Health, Labour, and Welfare.

##### (2) Information from the emergency report

Information on "self-harmed" individuals transported by ambulance in the 3 years prior to the study was collected from the emergency reports of ambulance service.

##### (3) Demographic information

A total population count in the regions in the 3 years prior to the study was recorded by sex and 5-year age group by each local governments.

##### (4) Regional characteristics

The following information was collected from published statistical data sources: geographic information, proportion of unmarried individuals, widowed spouses, divorcees, nuclear families, the unemployed, individuals in the labor force, and the annual population turnover in the regions.

##### (5) Suicide prevention programs in existence prior to the study

Baseline information concerning suicide prevention programs implemented in each region 3 years prior to the study will be recorded by each regions.

#### Intervention program process monitoring

Every 6 months, each regional leader will collect information regarding the implemented projects described in the intervention program manual.

#### Data collection during the study

##### (1) Information on suicides

After consent is obtained for the use of designated statistics for other purposes, information regarding the number of suicides in the participating regions will be collected. Death certificates from the Vital Statistics records from 2006, 2007, 2008, and 2009 for the intervention and control regions will be used to collect the following data items: International Classification of Diseases 10th Revision (ICD-10) code for intentional self-harm (ICD-10 codes X60–X84), residence of individuals who committed suicide (municipality codes), cause of death, external cause of death (ICD-10 code), measure of suicide (ICD-10), sex, age, reported place (municipality codes), and identification number.

##### (2) Information regarding suicidal behavior

Information regarding "self-harmed" individuals transported by ambulance will be collected from emergency reports.

The following information will be collected regarding "self-harmed" individuals every 6 months: type of transportation, date of notification, residence address, destination address, incidence location, severity (death, severe, moderate, mild, other), sex, age, and means of self-harm infliction.

##### (3) Demographic information

Total population numbers in the regions will be collected every year between 2006 and 2009.

##### (4) Information regarding ongoing suicide prevention programs

Information regarding the existence and implementation of suicide prevention programs in each participating region will be collected every 6 months.

#### Responsibility for data collection

Regional leaders are responsible for collecting data from each municipality and sending the data set to the data management center in a timely manner.

#### Data management

Collected data will be exclusively managed by the data management center. The data set will comply with the data management procedures and the Personal Information Protection Law. The data set will be periodically duplicated and saved as a backup file.

### Outcomes

#### Primary outcome

The incidence of suicidal behavior (completed suicides and suicide attempts excluding mild cases reported on emergency reports).

#### Secondary outcomes

(1) Incidence of completed suicides.

(2) Incidence of suicide attempts.

### Statistical analysis

#### Primary analysis

In the primary analysis, the incidence of suicidal behavior will be calculated based on the number of suicidal behavior per person-year for the annual population. Data obtained will include the incidence of suicidal behavior and its 95% confidence intervals adjusted by sex, 5-year age group, and regional characteristics. This data will be compared between the intervention and control regions in "Group 1".

The significance level will be set at 0.05 for the two-sided test, and will be adjusted in the final analysis based on the methods of O'Brien and Fleming [12] for interim analysis.

Additionally, regression analysis will also be performed to examine the interactions among sex, 5-year age group, and regional characteristics. A statistician in the study group will determine the analysis plan, whereas a different independent statistician will perform the interim analysis. The independent statistician will not contribute to the revision of the statistical analysis plan after interim analysis.

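### Regions are allocated, but power and the primary incidence rest on person-years with no between-region variance, so the stated 5% error and the stated power over 80% cannot both be relied on

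*Protocol article*

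**What the plan says.** **Allocation.** The Abstract describes seven intervention regions, each with accompanying control regions. Under Participating regions and sample size estimation, "intervention and control regions will be selected based on the similarity in community characteristics and the incidence of suicidal behavior". The primary comparison is in Group 1: "Group 1: Regions in Aomori, Akita, Iwate, and the Minamikyushu area, with a total population of 670,000 individuals".

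**Power.** Rationale for estimation of sample sizes claims power over 80% in each group. It ties this to person-year incidences and says that the sizes are not adjusted for age, sex or regional characteristics. The same claim is repeated at a final two-sided level of 4.9%.

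**Analysis.** Under Primary analysis, "the incidence of suicidal behavior will be calculated based on the number of suicidal behavior per person-year for the annual population". The result is to be reported with "its 95% confidence intervals adjusted by sex, 5-year age group, and regional characteristics". Baseline Information, item (4), lists the regional data collected, which are geography and "proportion of unmarried individuals, widowed spouses, divorcees, nuclear families, the unemployed, individuals in the labor force, and the annual population turnover in the regions". The article does not say which of these enter the primary model.

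**Error rate.** The section on interim analysis says that the O'Brien-Fleming adjustment keeps the two-sided type I error at 0.05.

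**The concern.** The intervention is given to regions, so the intervention effect can be no more precise than the variation between regions allows. Person-year (Poisson) error measures only chance variation in counts within a fixed rate. If regions differ in their underlying rates for reasons other than the programme, a test on person-year error is too liberal and its interval too narrow. An O'Brien-Fleming boundary does not correct this, because it controls repeated looks and not a wrong variance.

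At stake are the primary p-value and interval, and also the interim look, which can lead to a recommendation to stop or revise the study. The Secondary analysis section carries the same plan to Group 2 and to both groups combined.

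**Working it through.** **Inputs from the article.** Group 1 has 670,000 people in four areas and Group 2 has 1,450,000 in three. Table 1 gives control suicide rates of 30 and 20 per 100,000, ambulance transports at 50% of suicides, reductions of 20% and 15% over 3 years, and a two-sided 5% level.

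**Assumptions, not in the article.** A 1:1 population split; regions of equal size; one intervention and one control region per area, so 4 against 4 in Group 1; and a residual between-region coefficient of variation k, after matching and adjustment.

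**Step 1: reproduce the stated power.** SE = √(1/E0 + 1/E1); power = Φ(|ln RR|/SE − 1.96).

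- Group 1: 335,000 × 3 = 1,005,000 person-years per arm at 30 × 1.5 = 45 per 100,000. E0 = 452 and E1 = 362. SE = 0.0705; 0.2231/0.0705 = 3.16; power 88.6% (88.4% at 4.9%).
- Group 2: 725,000 × 3 = 2,175,000 person-years per arm at 20 × 1.5 = 30 per 100,000. E0 = 653 and E1 = 555. SE = 0.0578; 0.1625/0.0578 = 2.81; power 80.3% (80.1% at 4.9%).

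Both agree with the claim, with no between-region variance in the formula. Intervention shares of 30% to 60% leave Group 1 at 81% to 88%. With completed suicides alone, power is 73% and 63%, so the stated figure needs the composite rate.

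**Step 2: type I error if person-year error is used.** Under the null, the Poisson variance of the log rate ratio is vP = 2/E0, and regions add vB = 2k²/c, with c regions per arm. The true two-sided error is 2[1 − Φ(1.96 × √(vP/(vP + vB)))].

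Group 1 at k = 0.10: vP = 2/452 = 0.0044 and vB = 2(0.01)/4 = 0.0050. The root is 0.685, so the effective critical value is 1.34 and the error is 17.9%.

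| k | Group 1, E0 = 452 | Group 1, suicides only, E0 = 302 |
|---|---|---|
| 0.05 | 8.4% | 7.2% |
| 0.10 | 17.9% | 13.9% |
| 0.15 | 29.8% | 23.3% |

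The second column is a lower bound on events. It is shown because Table 1's 50% ratio is labelled as severe and mild cases, while the primary outcome excludes mild ones.

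**Step 3: power if region-level error is used.** With variance 1/E0 + 1/E1 + 2k²/4 and t critical values of 3.18 (3 df, area pairs) or 2.45 (6 df, unpaired), Group 1 power is:

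| k | 3 df | 6 df |
|---|---|---|
| 0 | 57% | 75% |
| 0.05 | 49% | 66% |
| 0.10 | 34% | 47% |
| 0.15 | 24% | 32% |

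Even with a normal critical value, Group 1 falls to 80.7% at k = 0.05 and 60.8% at k = 0.10. Group 2 has almost no margin: at k = 0.01 the variance rises from 0.003336 by 2(0.0001)/3 = 0.000067, and power is 79.6%.

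**Step 4: room for regional covariates.** Eight regions with an intercept and an intervention term leave 6 df. Each separate region-level covariate costs one: five leave 1 df, six leave none, and with seven or more the intervention effect is not estimable. Item (4) lists eight characteristics, but as data collected.

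**The case against.** The strongest reply is that an incidence per person-year defines a rate, not a variance. A person-year offset is compatible with a random region effect, area strata or overdispersion. The article names no model for the primary interval and leaves the plan to a study statistician, and that plan is not shown. This stands: it cannot be said that the primary interval is wrong as planned, or that the matching will be ignored.

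It does not rescue the article, because its two fixed statements pull apart. If the unseen plan keeps person-year error, the claim to hold 5% fails for any k above zero. If it adds region-level error on about eight regions, the power claim fails even at k = 0.

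A reader might also infer that the primary model holds about eight regional covariates on eight regions, so that the effect cannot be estimated. The documents do not support this. The list is of data collected, the number of model terms is not given, and eight regions is itself an inference. Suicide data carry municipality codes and are collected from municipalities. If municipalities were the units, there would be more degrees of freedom than in Steps 3 and 4, though variation between them would still need a place in the error.

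Finally, k is not in the article, and matching and adjustment will reduce it. This too stands, which is why k is defined as residual and shown as a range.

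**Conclusion.** The point holds in limited form. The stated power rests on independent person-years although regions are allocated, and no between-region variance is stated. Conditional on person-year error in the test, the Group 1 type I error is about 8%, 18% and 30% at residual CVs of 0.05, 0.10 and 0.15, or about 7%, 14% and 23% with the fewest plausible events. Conditional on region-level error with 4 against 4 regions, Group 1 power is at most 57% to 75% under Table 1's own assumptions.

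The power reproduction and the inconsistency are firm, given a roughly even population split. The sizes depend on the assumed CV and on the inferred number of regions. Regional adjustment does not stand in for a region-level error term, and about eight regions can support very few such covariates. Non-estimability is a risk only if seven or more enter separately, which the article does not say.

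**What to change.** State the region as the unit of inference and give the number of regions per arm in each group. Then:

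- Keep the person-year offset and add strata for the matched areas.
- Base the test and interval on region-level error, through a random region effect, overdispersed counts or a paired analysis of the area log rate ratios, with small-sample degrees of freedom. Use the same variance for the interim boundary.
- Limit the primary adjustment to sex, age group and baseline incidence, for which three years of data are already collected. Keep the other regional characteristics for sensitivity analyses.
- Restate power over a range of between-region CV. Baseline data by region could inform that range.

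Other short, prespecified covariate sets would also be defensible; what matters is that the set is fixed before any comparison by arm. No new data are needed. The cost is wording and modelling time, wider intervals, and a stated power below 80% if there are only about eight Group 1 regions.

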#### Interim analysis and rules for stopping or revising the study protocol

The interim analysis in "Group 1" will be performed 2 years after the study's implementation to evaluate the achievement of the primary objectives. Multiplicity will be adjusted using the methods of O'Brien and Fleming, in order to maintain Type-1 error at 0.05 for the two-sided test. The results will be reported to the Central Research Ethics Committee, which is expected to make recommendations to the J-MISP director to either stop the study or revise the study protocol if the primary objective of the study has already been achieved or is unlikely to be achieved.

#### Secondary analysis

In addition to the primary analysis, it will also be evaluated whether the primary outcome (the incidence of suicidal behavior) is also significantly reduced in intervention regions of "Group 2" areas, as a consequence of implementation of the program, when compared to control regions. The incidence of suicidal behavior will be investigated in Groups 1 and 2 combined. The analysis will be performed using the primary analysis plan described above.

Secondary outcomes will also be examined in order to determine whether the rate of completed suicides and suicide attempts – including individuals with severe, moderate, and mild self-harm transported to a hospital – is significantly reduced in the intervention regions, when compared to the control regions in "Group 1" and "Group 2". The same will be examined for both groups combined.

Subgroup analysis of the primary and secondary outcomes will be performed by sex, 5-year age group, and regional characteristics in "Group 1", "Group 2", and both groups combined. In addition, the incidence of suicidal behavior adjusted by sex and 5-year age group in the intervention and control regions will be calculated using the model population in 1985 as a reference population. Because of the exploratory nature of the secondary analysis, no adjustment for multiplicity will be made.

### Ethical considerations

The rights and welfare of the participating residents will be protected according to the World Medical Association Declaration of Helsinki Ethical Principles for Medical Research Involving Human Subjects. The study will comply with the ethical guidelines of the Ministry of Education, Culture, Sports, Science and Technology, as well as the Ministry of Health, Labour, and Welfare. Ethical validity, including safety, scientific legitimacy, and the reliability of results are to be ensured. This study will also comply with the ethical guidelines for epidemiologic studies and the Personal Information Protection law. The NOCOMIT-J principal investigator and the J-MISP director will be responsible for the protection of personal information during the study.

The data collected in this study will not include personal identification that would enable individuals to be identified. The data management center will collect only anonymous data.

### Stopping of the study

The J-MISP director is to inform the principal investigator of the NOCOMIT-J of the decisions of the Central Research Ethics Committee in the cases described below to discuss whether the study in each region or all of them should be discontinued.

a) The results of the interim analysis do not satisfy the standards set by the committee.

b) Safety issues that might affect the conduct of future studies arise from the results of interim analysis or the results of periodic monitoring.

c) The Local Research Ethics Committee of a region retracts consent to participate.

### Revision of the study protocol and due process

The J-MISP director is to inform the NOCOMIT-J principal investigator of the decisions of the Central Research Ethics Committee as soon as possible, when the Central Research Ethics Committee recommends that the study be redesigned due to the emergence of safety issues based on the interim analysis, periodic monitoring, and/or emergence of serious issues that might affect the conduct of future studies. The J-MISP director is to call a meeting of the study group and discuss the revision of the study protocol. If a recommendation to revise the study protocol is made, the principal investigator of the NOCOMIT-J will propose the revised study protocol as soon as possible and submit the proposal to the J-MISP director.

The J-MISP director will deliberate and approve the proposal at the Central Research Ethics Committee meeting and adopt the revision of the study protocol after deliberation in the steering committee. The study group management office will inform all of the participating researchers, and regional leaders will submit the proposed revision to the Local Research Ethics Committee and local government in each of the participating regions. The revision of the study protocol is to be implemented when approved.

### Study monitoring

#### Periodic monitoring

The regional leaders will periodically (once every 6 months) submit reports evaluating the progress of the study to the intervention program committee. The intervention program committee will submit a process evaluation monitoring report to the study group management office and J-MISP administration office once every 6 months. The J-MISP administration office will consider the progress of the research and submit the process evaluation monitoring report to the progress control committee and the Central Research Ethics Committee of the J-MISP.

The data management center will submit an event monitoring report to the J-MISP administration office. The office will submit event monitoring reports to the progress control committee, Central Research Ethics Committee, and the study group management office. The event monitoring report, which will contain the results of the analysis separated by intervention and control groups, will be submitted to the progress control committee and Central Research Ethics Committee. The results of the data analyzed from both groups combined will be submitted to the study group management office.

The progress control committee will examine the monitoring reports and submit the evaluation to the J-MISP director. The Central Research Ethics Committee will examine the monitoring reports as a third party, and make recommendations to revise the study protocol or discontinue the study to the J-MISP director when and if ethical problems, such as safety and efficacy issues, arise.

